### Setting

The study will be conducted in urban slums of Lucknow, a heavily populated area of North Central India. There is one slum, or *'anganwadi'* for a population of approximately 1000 economically disadvantaged persons. The criteria for selecting an area for an urban slum are that it does not have the basic amenities of sanitation and water supply and the income of its residents is below the national poverty level. To ensure primary health care of children under five years of age, all the urban slums in Lucknow are covered by the national Integrated Child Development Scheme (ICDS). Through the ICDS, there is one informal health worker, the *'anganwadi'* worker per slum and the entire slum population is registered with her. There are 203 slums within urban Lucknow. These will be listed alphabetically and given a serial number. After generating a random digit table with 55 number, the first slum will be randomized to either one intervention type by toss of coin, and then every alternate slum having the same serial number as that in the random digit table will receive this intervention, the rest the other. Thus, 50 slums will be randomly allocated, 25 to each of the two arms of the trial.

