### Variables

The main outcome measures are weight and height. The project workers will measure these on the day of the visit, once every six months. To ascertain age of the hild, date of birth will be abstracted from the register of the '*anganwadi'* worker. For those who cannot be contacted at the time of the visit but were not reported as dead, a second visit will be made to ascertain the reason for loss to follow-up. Parents of dead children will be contacted to ascertain the cause of death.

The weight of the child will be measured in kilograms to the nearest 100 grams and the standing height was measured in centimeters to the nearest millimeter. It will not be possible to blind the data collectors or the parents to the intervention type. However, the data collectors did not have information of the previous weight or height of the children. Approximately 10% of the data will be validated by different project workers within 1 week. The validators will be blind to all the anthropometric data on the subjects.

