### Sample Size and Data Analyses

Sample Size: Sample size was calculated for a continuous outcome. For a standardized effect size of 0.1, with a power of 80% and an alpha level of 0.05, using a 2-tailed t test, taking into account design effect, about 2000 children will be included in each arm.

Data Analysis:EPI6.1 statistical software will be used to calculate at baseline, weight for age (WA), height for age (HA) and weight for height (WH) z scores, when compared to the nutritional standards of the World Health Organization. Baseline distribution of undernutrition (weight for age (WAZ) z score < - 2 standard deviations (S.D.)), stunting (height for age (HAZ) z score < - 2 S.D.) and wasting (weight for height (WHZ) z score < - 2 S.D.) will be calculated for all the enrolled children. Weight by age will be calculated for all the enrolled children using the 1994 data of the first survey. Univariate analyses will be done to compare age, sex and history of passage of worms and weight and height in 25 control areas and 25 albendazole areas using the chi square test for categorical and student's t test for continuous variable.

Because randomization will be by area, we will assess the area specific weight gain and height gain in each group. We will report area specific averages, taking one result per area. Height and weight gain in one year and two years will be compared in 25 control versus 25 albendazole areas.

In subgroup analysis, weight and height gains will be calculated for children who are underweight, stunted and wasted at enrollment in the control and ABZ groups. We will also compare 2-year changes in the proportion of underweight, stunted and wasted in the two groups.

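### The main comparison of area-average gains makes no adjustment for age, sex or starting size, which is valid but gives up some precision in a trial with little to spare

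*Protocol*

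**What the plan says.** Under Setting, the Protocol states that "50 slums will be randomly allocated, 25 to each of the two arms of the trial". Under Variables, "The main outcome measures are weight and height", measured every six months, with date of birth taken from the slum register. The primary objective is gain in both at two years, in children aged 1 to 5.

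Under Sample Size and Data Analyses, the comparison is built on area summaries: "We will report area specific averages, taking one result per area", followed by "Height and weight gain in one year and two years will be compared in 25 control versus 25 albendazole areas". No covariate appears in that comparison.

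The same section does use the baseline data elsewhere. They give the z scores and the prevalence of undernutrition, stunting and wasting. They enter univariate comparisons of the arms, and they define the subgroups by nutritional status at enrollment. Baseline weight and height also enter the gain by subtraction. Beyond that, none of them adjusts the main comparison.

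The sample size is stated as "For a standardized effect size of 0.1, with a power of 80% and an alpha level of 0.05, using a 2-tailed t test", and "taking into account design effect, about 2000 children will be included in each arm". No design effect or ICC is given.

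**The concern.** Children between 1 and 5 grow at different rates according to age, and probably according to sex and starting size. A gain score subtracts the starting value, but it leaves any remaining dependence of growth on that value and does nothing about age or sex. That explainable variation stays in the area means. With one result per area, the spread of those means is the only error term, so it widens the confidence interval for the arm difference.

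The stake is precision. The sample size leaves little room for clustering, and the variables that could recover some precision are already being collected. Testing them for balance between arms recovers none of it.

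**Working it through.** **Inputs from the Protocol.** Effect 0.1 SD, 80% power, two-sided alpha 0.05, about 2000 children per arm, 25 areas per arm. Derived: 2000/25 = 80 children per area.

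**Assumed, because the Protocol gives no value.** The ICC; the correlation r between baseline and follow-up; the ratio k of follow-up SD to baseline SD; how far covariates explain variation between areas. The 0.1 is read as SDs of the analysed gain.

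**Step 1: the plan's own figure.** Without clustering, n = 2(1.960 + 0.842)²/0.1² = 1570 per arm. The stated 2000 then implies a design effect of 2000/1570 = 1.274 and an ICC of 0.274/79 = 0.0035. This is back-calculation. It neither confirms nor refutes the 2000, because the design effect used is not stated.

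**Step 2: unadjusted power.** In SD units, Var(area mean) = ICC + (1 − ICC)/80, and SE = √(2 × Var/25). Power comes from a noncentral t on 48 df.

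- ICC 0.0035: Var = 0.00347 + 0.01246 = 0.01592, SE = 0.0357, power 78.4% (80.0% by the normal approximation). The child-level share of the variance is 0.01246/0.01592 = 78%.
- ICC 0.01: Var = 0.01 + 0.012375 = 0.022375, SE = 0.0423, power 63.9%. The child-level share is 55%.
- ICC 0.02: power 48.8%.
- ICC 0.05: power 28.6%.

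**Step 3: how much baseline adjustment removes.** With baseline SD set to 1, gain has variance 1 + k² − 2rk, and the variance left after regression on baseline is k²(1 − r²). The ratio is

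k²(1 − r²)/(1 + k² − 2rk).

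When k = 1 this reduces to (1 + r)/2:

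| r | k = 1 | k = 1.1 |
|---|---|---|
| 0.6 | 0.80 | 0.87 |
| 0.7 | 0.85 | 0.92 |
| 0.8 | 0.90 | 0.97 |
| 0.9 | 0.95 | 1.00 |

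So the reduction is 5 to 20% with equal SDs. It vanishes whenever rk = 1, for example r = 0.8 and k = 1.25: 1.5625 × 0.36/(1 + 1.5625 − 2) = 0.5625/0.5625 = 1. These ratios cover the baseline value only. Age and sex could add to them by an amount the Protocol does not allow one to estimate.

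**Step 4: power after a 5 to 20% reduction.** In the first adjusted column only the child-level term is reduced; in the second both terms are reduced by the same share.

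| ICC | Unadjusted | Within-area only | Within and between |
|---|---|---|---|
| 0.0035 | 78.4% | 80.0-84.8% | 80.4-86.6% |
| 0.01 | 63.9% | 65.1-69.0% | 66.1-73.5% |
| 0.02 | 48.8% | 49.5-51.9% | 50.8-57.8% |
| 0.05 | 28.6% | 28.8-29.5% | 29.8-34.4% |

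**The case against.** **Covariate choice is usually left to the SAP.** The Protocol nowhere calls its comparison unadjusted, and an SAP that is not shown could add adjustment. This stands as a limit. But the Protocol does not leave the main analysis open: it states the summary, the unit and the contrast, and the plain reading is a comparison of raw area averages.

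**Nothing planned is wrong.** This also stands. A reader might infer that the comparison is biased, or that a chance difference in age mix between arms corrupts the estimate. The documents do not support that. Areas are the unit of both randomization and analysis, so chance imbalance is already reflected in the between-area standard error, and about 80 children per area average out much of the individual age variation.

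**Gain is what the primary objective asks for.** True, but adjustment does not change it. Regressing the two-year value or the gain on baseline leaves the same residuals, so the adjusted contrast is still a difference in gain.

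**The benefit may be small.** This stands in part. A reader might take 5 to 20% as an assured saving, but it requires equal SDs, which nothing in the Protocol supports for growing children, and it can be nil. The upper power figures also need covariates to explain variation between areas as well as within them. A reader might further infer that the baseline data serve only to test balance; they also feed z scores, subgroups and the gain itself.

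**Conclusion.** The point holds as a modest loss of efficiency, not a flaw in validity. The main comparison names no adjustment for age, sex or baseline size, although all are recorded and are likely to predict gain in this age range.

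Under equal SDs and an assumed r of 0.6 to 0.9, baseline adjustment alone is worth roughly 2 to 8 percentage points of power at the implied ICC of 0.0035, and 1 to 10 points at an assumed ICC of 0.01. The spread reflects whether between-area variance falls too. At an ICC of 0.05 the benefit is under 1 point if only within-area variance falls, and at most about 6 points otherwise. Age and sex may add to these figures; a larger follow-up SD may reduce the baseline component to nothing.

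One might infer that adjustment would make good a sample size with little allowance for clustering. It would not: at an ICC of 0.01 or more, every adjusted figure in the table stays below 80%. The change is worth making because it is likely to help and needs no new data.

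**What to change.** Keep one result per area, but make it an adjusted one. In Sample Size and Data Analyses, state that:

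- two-year weight will be regressed on baseline weight, age and sex across all children, ignoring arm, and likewise two-year height on baseline height, age and sex;
- the residuals will be averaged by area, and the 25 albendazole and 25 control area means compared with a t test on 48 df;
- the covariates are fixed in advance and not chosen from the univariate comparisons of the arms;
- the unadjusted area averages of gain will be reported in a supporting table.

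The one-year comparison can be handled in the same way. If an SAP already specifies such an adjustment, the Protocol should refer to it.

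The cost is a few lines of text. No new data, visits or areas are needed, and the area remains the unit of analysis.
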